### Primary outcome measures

#### Safety

The number of serious adverse events (SAEs; DVT, pulmonary embolism and elevated serum creatine kinase concentration (creatine kinase > 3800 IU/L)) will be compared between the control and intervention groups.

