### Recruitment and randomisation process

All sequential ICU admissions will be screened for eligibility. Eligible patients with mental capacity for informed consent will be approached, the risks and benefits of participation explained and written informed consent will be obtained before enrolment by the investigator physician. However, we envision that the majority of eligible patients will be receiving invasive mechanical ventilation and requiring sedation, and thus lacking capacity to consent. In this instance, declaration of agreement will be sought from the patient’s ‘Personal Consultee’ who may be a representative, partner or close friend. Once the participant recovers and is capable of understanding the details of the trial, they will be approached to provide their informed consent retrospectively. If the patient chooses to withdraw from the trial, they will be given the choice of having their existing data and samples destroyed or excluded from final analysis.

Upon informed consent or declaration of agreement, eligible patients will be randomised to either the intervention arm or the control arm in a 1:1 ratio. Separate randomisation lists have been prepared for each site by an independent statistician and uploaded to the study electronic data capture system PROMASYS (Surrey Clinical Trials Unit). In addition, the randomisation list and corresponding envelopes containing randomisation assignments will be stored in the trial file. Randomisation, outcome measure assessments and RVOS intervention will be performed by a research assistant unblinded to patient allocation.

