**Fig. 2 Fig2:**
[figure not shown]
Schedule of study procedures and outcome measure assessments. DVT deep vein thrombosis, EDTA ethylenediamine tetraacetic acid, ICU intensive care unit, RVOS repetitive vascular occlusion stimulus, SF-12 12-Item Short Form Health Questionnaire

If the participant is randomised to the intervention, one RVOS session will be carried out after baseline assessment on day 1. Arterial blood samples will be collected 3 and 24 h after RVOS and at the same time points after baseline assessments in control participants. From day 2, intervention participants will receive two RVOS sessions per day until day 10 of enrolment or until ICU discharge if this occurs before day 10.

Outcome measure assessments of muscle mass and quality, arterial function, muscle strength, physical function, and blood and urine biomarkers will be repeated on days 6 and 11 of study enrolment. Clinical data including blood results, nutritional and organ support, severity of illness, fluid balance, physiotherapy interventions and specific drug treatment (neuromuscular blocking drugs, corticosteroids, statins and propofol) will be recorded daily from days 1 to 11 of enrolment. At ICU and hospital discharge, physical function and muscle strength assessments will be repeated. In addition, at hospital discharge, an acceptability interview will be conducted with the participant and personal consultee, and blood and urine samples collected. Study participation will end upon completion (by telephone) of the SF-12 health questionnaire 3 months after hospital discharge.

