### Repetitive vascular occlusion stimulus (RVOS) intervention

Participants in the intervention arm will receive one session of RVOS treatment on day 1 and two sessions per day, at least 4 h apart, from day 2 to 10 of study enrolment or until ICU discharge if this occurs before day 10. For safety, the intervention leg will be examined daily before the first RVOS session for deep vein thrombosis (DVT) from the common femoral to popliteal vein using ultrasound (CX50 Philips Ultrasound with L12–3 linear array transducer). If DVT is suspected, RVOS or arterial assessment will not be performed and the clinical team will be notified immediately.

During the RVOS session, the participant will lie supine in a semi-recumbent position with the lower limbs extended. A pressure cuff (SC12LTM segmental pressure cuff; Hokanson, Bellvue, WA, USA) will be applied around the proximal right thigh with a bandage wrapped underneath to avoid skin irritation and bruising. Each RVOS session will last for 40 min and will include four cycles of 5 min cuff inflation to 50 mmHg above the average systolic blood pressure to completely occlude arterial flow distally to the limb [98], followed by 5 min of complete deflation (0 mmHg) (Fig. 3). Pressure in the pneumatic cuff will be controlled by an inflator and air source device (E20 Rapid Cuff Inflator and AG101 Cuff Inflator Air Source; Hokanson). Maximum cuff pressure will be 200 mmHg.

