### Statistical analysis

The statistical analysis addresses the objectives of demonstrating the safety and tolerability of applying RVOS to the lower proximal limb of ICU patients, and assessing the feasibility of undertaking a larger-scale study to demonstrate efficacy. As a feasibility trial, the statistical analysis will primarily be exploratory in nature, and thus hypothesis generating rather than confirmatory.

The primary objective of safety will be evaluated based on the frequencies and percentages of adverse events categorised by severity, group and site. The tolerability will be evaluated by assessing VAS pain scores of the intervention arm at each time point in terms of means and standard deviations.

The main feasibility outcome of recruitment will be evaluated as the percentage of randomised participants out of total eligible patients. The number of participants randomised as a percentage of targeted recruitment will also be computed. If data are available, the average number of research assistants’ hours spent on recruiting one participant will also be computed. Retention will be evaluated as the proportion of participants remaining at each time point compared to the number recruited in each arm.

Descriptive statistics will be used to summarise all response variables by site, time point and treatment group. Means and standard deviations will be computed for continuous outcomes and frequencies and percentages will be computed for categorical/dichotomous outcomes. The relationship with potential confounding factors—such as site, demographic data, delirium during ICU stay, severity of illness, length of ICU stay, sepsis (defined using SOFA score), and use of drug treatment (such as corticosteroids, neuromuscular blocking drugs, statins and propofol)—will be explored.

The following inferential statistics will be performed strictly for the purpose of identifying the directions and magnitudes of effects rather than to evaluate the statistical significance of the results due to inadequacy of statistical power.

Outcome measures recorded at a time point (such as ‘timed up and go’ and ‘sit to stand’ assessment) and clinical outcomes (such as duration of mechanical ventilation and length of ICU and hospital stay) will be compared between the two arms using an independent-sample *t* test.

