### Serious adverse events

Safety reporting will be performed in accordance with HRA guidelines for non-CTIMP research (not involving investigational medicinal products or medical devices) with adherence to GCP standards. Untoward medical occurrences are expected in critically ill patients and their monitoring and treatment is considered standard care. As a result, only serious adverse events (SAEs) will be reported. These are defined as any untoward occurrence that results in death; is life-threatening; requires hospitalisation or prolongs existing hospitalisation; or results in persistent or significant disability/incapacity; or any other important medical event that required intervention to prevent the outcomes already listed based upon appropriate judgement by the investigators.

SAEs will be recorded from when participant consent is obtained to 3-month follow-up after hospital discharge. SAEs possibly, probably and definitely related to the study, such as DVT, pulmonary embolism and elevated creatine kinase (creatine kinase > 3800 IU/L), will be recorded. For all SAEs, the following data will be recorded in the eCRF and patient notes: description; date and time of occurrence; severity; relationship of SAE to study procedure (determined by the investigator physician); treatment required; and action taken with research procedure. The completed SAE form, signed by the reporting investigator and Principle Investigator of the site, will be submitted to the sponsor within 24 h of becoming aware of the event and all SAEs will be followed-up until resolved. If unexpected serious related event occurs, the Chief Investigator will notify Principle Investigators at local sites and the research ethics committee within 15 days of the event.

In the case of unanticipated concerns of safety to study participants or availability of new data arising from clinical or preclinical studies with this intervention, the study will be paused during review of newly available data prior to a final decision for continuation or termination of the study. If, in the opinion of the Chief Investigator, the clinical events indicate that it is not justifiable to continue the trial, the TSC will terminate the trial following consultation with the sponsor.

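### DVT counts are compared between arms, but daily ultrasound is described only for the RVOS leg; the SAE start point and the AE/SAE wording also need reconciling

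*Protocol article*

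**What the plan says.** **Outcome.** Primary outcome measures, Safety, takes the number of SAEs (DVT, pulmonary embolism, creatine kinase above 3800 IU/L) and says that it "will be compared between the control and intervention groups".

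**Search for DVT.** The section on the RVOS intervention says that "the intervention leg will be examined daily before the first RVOS session for deep vein thrombosis (DVT"), by ultrasound. It continues: "If DVT is suspected, RVOS or arterial assessment will not be performed and the clinical team will be notified immediately". The text describes no DVT scan of control patients or of the untreated leg. The caption of the schedule figure reads "Schedule of study procedures and outcome measure assessments. DVT deep vein thrombosis", so DVT appears somewhere in that figure.

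**SAE window.** Under Serious adverse events, "SAEs will be recorded from when participant consent is obtained to 3-month follow-up after hospital discharge". The recruitment section expects most eligible patients to be sedated and to lack capacity. They enter on a personal consultee's declaration of agreement, and after recovery "they will be approached to provide their informed consent retrospectively". Randomisation follows either route, and RVOS starts on day 1.

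**Event type.** Under Statistical analysis, safety is evaluated on "frequencies and percentages of adverse events categorised by severity, group and site". Under Serious adverse events, "only serious adverse events (SAEs) will be reported".

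**The concern.** A daily scan finds DVTs that clinical suspicion would miss. As a safety check before cuff inflation the scan is not in question. The difficulty is that what it finds enters a count that is then set against an arm for which no such search is described. Even if RVOS caused no DVT, the RVOS arm would be expected to show more.

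The result has consequences. The Discussion makes a larger trial conditional on RVOS being shown safe, and the Trial Safety Group sees safety data after every five patients. An artefact of detection could influence both.

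The other two conflicts concern completeness. If the SAE window opens only at the participant's own consent, events during much of the RVOS period fall outside it, and patients who die before regaining capacity never enter it. If only SAEs are collected, non-serious local effects of the cuff have no stated route into the adverse-event table.

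**Working it through.** The article gives no figure for the safety comparison, so there is none to reproduce. What follows illustrates the size of the bias.

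**Inputs**
- True DVT rate p = 0.10 in both arms (Discussion, figure for critically ill patients), so RVOS has no effect.
- n = 16 per arm (Sample size rationale, ICU survivors). The ratios do not depend on n.
- Detection by daily scan s = 0.95 (assumption).
- Detection on clinical suspicion c = 0.20 to 0.50 (assumption).
- Share of DVTs lying in the scanned leg L = 1 or 0.5 (assumption).

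**Formulas**
- Expected RVOS count = n × p × [L × s + (1 − L) × c]
- Expected control count = n × p × c
- Spurious ratio = [L × s + (1 − L) × c] / c

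| L | c | RVOS | Control | Ratio |
|---|---|---|---|---|
| 1 | 0.50 | 16 × 0.10 × 0.95 = 1.52 | 0.80 | 1.90 |
| 1 | 0.20 | 1.52 | 0.32 | 4.75 |
| 0.5 | 0.50 | 16 × 0.10 × (0.475 + 0.25) = 1.16 | 0.80 | 1.45 |
| 0.5 | 0.20 | 16 × 0.10 × (0.475 + 0.10) = 0.92 | 0.32 | 2.88 |

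With the same search in both arms the ratio is 1. Scanning is tied to RVOS sessions, so it stops at day 10 or ICU discharge. Later DVTs would be found clinically in both arms, which pulls the ratio over full follow-up towards 1.

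**How often would an excess appear?** These are exact binomial probabilities with 16 per arm, p = 0.10 and every RVOS-arm DVT found. The chance that the RVOS arm has more DVTs is 38% when all control DVTs are also found (24% tie), 47% when 75% are found, 57% when 50% are found, and 69% when 25% are found.

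**SAE window.** Side by side, the recruitment section separates the participant's informed consent from a consultee's agreement and randomises on either, while the SAE section opens the window at participant consent. If the anticipated 30% mortality is read as death in ICU, reaching 32 survivors takes about 32 / 0.70 = 46 patients, of whom about 14 die. Those who die before regaining capacity would, on the literal wording, contribute no SAE, not even the death. The rule is the same in both arms.

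**Event type.** Severity is recorded in the eCRF for all SAEs, so the planned table can be filled for SAEs. Non-serious events are the part with no stated source. The Discussion cites literature rates of 13.1% for bruising and 4.4% for petechiae, and the leg is examined after every session, so such findings may well be seen.

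**The case against.** **Were controls really not scanned?** A reader might infer that control DVTs are found only on clinical suspicion. The article does not say so. It is silent, which is weaker. The sentence on suspected DVT also names arterial assessment, which uses a thigh cuff and is planned in both arms at baseline, day 6 and day 11. A check before that assessment in controls is plausible, and Fig. 2 has a DVT entry. What stands is that no daily search in controls is described.

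**Creatine kinase.** A reader might extend the point to CK, since daily monitoring is mentioned in the RVOS section. That sentence names no arm, and blood results are recorded daily on days 1 to 11 without restriction by arm. The documents do not support an imbalance in CK.

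**Consent wording.** The article uses consent loosely. The Consent row of Table 3 counts agreement by consultees, and a Trial Safety Group that is updated on any SAE fits poorly with a late start. The intended start may well be entry on either route. As written, the sections still conflict. Because the rule is common to both arms, it is a gap in capture and not in itself an imbalance between them.

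**Attribution and the adverse-event table.** A reader might infer that only related SAEs are kept, or that the table has no data at all. The SAE section lists the fields recorded for all SAEs, including severity and relationship to the study procedure. Controls also undergo study procedures. Neither inference holds.

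**Exploratory analysis.** The analysis is descriptive and hypothesis-generating. That limits what may be claimed, but it does not make unequally ascertained counts comparable.

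**Conclusion.** On the text, the between-arm DVT comparison is open to detection bias towards apparent RVOS harm. Under the stated assumptions the spurious ratio is about 1.9–4.8 if every DVT lies in the scanned leg and about 1.5–2.9 if half do. Only the 10% rate comes from the article; the detection shares and the split by leg are assumptions.

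It would be too strong to say that the trial will show an excess. With counts this small, and even with full detection in the RVOS arm, an excess there is 57–69% likely if half to a quarter of control DVTs are found, against 38% with equal search.

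The SAE start point contradicts the recruitment section and, read literally, loses events in both arms. The adverse-event wording in the analysis does not match SAE-only collection. These two are matters of capture and wording, and neither makes the arms unlike each other.

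**What to change.** Recruitment is complete, but the analysis plan is to be finalised before database lock, so the changes are to analysis and eCRF wording.

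1. **DVT.** Classify each DVT by how it was found: protocol scan or clinical suspicion. Report scan-detected DVT in the RVOS arm as a single-arm rate with an exact 95% CI (with 0 of 16, for example, the upper limit is 1 − 0.025^(1/16) = 20.6%).
2. **Comparison.** Compare arms only on DVTs found by a search made in both, for example any scan before arterial assessment at baseline, day 6 and day 11, if Fig. 2 confirms it. Otherwise show counts by arm and mode of detection, and do not read a difference as an RVOS effect.
3. **Avoid the opposite bias.** State that a clinically triggered count alone is not a neutral substitute. The daily scan finds RVOS-arm DVTs first and the clinical team is told at once, so those events drop out of such a count and RVOS harm is understated.
4. **SAEs.** Count all SAEs from randomisation for every participant, whatever the attribution. Medical notes are source documents, so earlier events can be abstracted.
5. **Adverse events.** Reconcile Statistical analysis with Serious adverse events, and tabulate the leg findings from the post-session examinations where they were recorded.

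The cost is some abstraction from notes and a less simple safety comparison with fewer DVTs in it. If Fig. 2 shows identical daily scanning in controls, the DVT point reduces to correcting the wording of the RVOS intervention section.

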#### Tolerability

The VAS pain score will be used to assess the tolerability of RVOS.

### Secondary outcome measures

#### Feasibility

Table 3 presents the pre-specified feasibility criteria that will be assessed.

**Table 3 Tab3:** Feasibility criteria of the study

Trial process	Outcome measure	Feasibility criteria
Screening	Percentage of potentially eligible patients being missed	< 55% of potentially eligible patients being missed
Consent	Percentage of personal consultee/participants agreeing to enrolment	> 75% of personal consultees/participants agreeing to enrolment
Recruitment rate	Number of patients recruited	Recruit 30 patients within 16 months
Randomisation	Demographic and severity of illness in the intervention and control arms	Balanced demographic and severity of illness in intervention and control arm participants
Delivery of intervention	Percentage of RVOS sessions performed out of the total possible sessions	80% of the scheduled RVOS sessions performed
Retention rate	Percentage of patients that remain on the ICU for the full 10 days of study enrolment	> 50% of enrolled patients remain on the ICU for the full 10 days of study enrolment
Outcome measure assessments	Percentage of outcome measure assessments performed within 24 h of the scheduled time Percentage of quality-of-life questionnaires completed at 90-day follow-up	100% of RFCSA ultrasound measurements performed within 24 h of the scheduled time > 75% of vascular, strength and functional capacity measures performed within 24 h of the scheduled time > 75% of surviving patients complete the quality-of-life questionnaires at 90-day follow-up
Electronic case report form data collection	Percentage of missing outcome and clinical data	< 10% missing outcome data including ICU and hospital length of stay and survival < 10% missing clinical data obtained from clinical medical notes and electronic patient records, such as severity of illness scores and requirement for organ supportive therapies

*ICU* intensive care unit, *RFCSA* rectus femoris cross sectional area, *RVOS* repetitive vascular occlusion stimulus

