### Secondary objectives

Our secondary objectives are to determine the feasibility of screening; obtaining consent and recruiting; randomising; retaining patients; delivering the trial intervention; performing outcome assessments and collecting data; assessing acceptability for patients, personal consultees (next of kin) and staff; and to determine outcome data characteristics to design a future larger trial.

In addition, we will explore any impacts on measures of muscle mass, quality and function (strength and physical function measures); vascular function; blood and urine biomarkers of muscle metabolism; vascular function; inflammation and DNA damage/repair mechanisms; and clinical outcomes to inform powering of any future prospective trial.

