### Sample size rationale

A total of 30 participants is recommended for pilot and feasibility trials [97]. To allow for balance in the stratification factors (gender and study site), a sample size of 32 participants was chosen, which will allow us to estimate a failure to deliver RVOS in the intervention arm of 30% to within a 95% confidence interval of ± 15.9%.

Based on an anticipated average rate of recruitment of 6 patients/month, 50% screening failure due to weekends, 20% decline of consent and 30% death before trial completion, we aim to recruit 1.6 patients per site per month. Recruiting from two sites, one starting 2 months after the other, is expected to yield 47 patients over 16 months. Recruitment will continue until 32 ICU survivors have been studied (16 patients in each group).

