Our study population has a high risk of hospital death and post-discharge mortality. This means that participants could be lost due to death before completion of the study, with previous reports of 30% mortality in a study with similar inclusion and exclusion criteria [109]. We will recruit until we have 32 participants that survive the ICU stay, recognising that subsequent deaths after ICU discharge may reduce the data available at hospital discharge and at 3-month follow-up.

We expect repeated inflation and deflation of the pneumatic cuff during the RVOS to cause minor fluctuations in heat rate and blood pressure. As a result, patients with profound cardiovascular instability (defined by infused vasopressors ≥ 0.5 μg/kg/min of norepinephrine or by opinion of the senior attending physician) will not be studied. Moreover, during the RVOS session, haemodynamic parameters will be monitored closely. Critically ill patients have a 10% incidence rate of DVT [110], whilst an incidence of 0.055% is reported in others who have received blood flow restriction exercise [92]. We will thus exclude patients with a history of DVT and pulmonary embolism (PE) as well as patients who have contraindication to pharmacological venous thromboembolism prophylaxis. Apart from an incidence of minor events such as skin petechiae (4.4%) and subcutaneous bruising (13.1%), no major bleeding risk of RVOS has been reported in the literature [92, 111]. However, as a safety measure, patients with profound coagulopathy (defined by > 2.5 times normal prothrombin time, > 2 times normal APTT, platelet count ≤ 50 or on IV heparin infusion APTR ≥ 2) will not be recruited or studied if this occurs.

If our pilot study shows that RVOS is safe, feasible and acceptable to apply to ICU patients, an appropriately-powered randomised controlled trial will be designed to assess any potential benefit of this procedure.

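### Table 3 judges the feasibility of randomisation only by baseline balance between arms, which can fail a correctly run randomisation and pass a faulty one

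*Protocol article*

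**What the plan says.** The protocol article, under Secondary objectives, states: "Our secondary objectives are to determine the feasibility of screening; obtaining consent and recruiting; randomising; retaining patients". Randomising is thus a feasibility objective in its own right.

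Under Feasibility, the article says "Table 3 presents the pre-specified feasibility criteria that will be assessed". The Randomisation row of that table has one outcome measure, "Demographic and severity of illness in the intervention and control arms", and one criterion, "Balanced demographic and severity of illness in intervention and control arm participants". The row gives no count of allocations made, allocation errors or use of the list. It does not define balance.

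The Sample size rationale names the stratification factors: "To allow for balance in the stratification factors (gender and study site), a sample size of 32 participants was chosen". Age and severity of illness are not among them. The section on recruitment and randomisation describes separate lists for each site and does not mention gender. The target is 32 ICU survivors, 16 per group, and recruitment "is expected to yield 47 patients over 16 months".

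The Discussion makes the later powered trial conditional: "If our pilot study shows that RVOS is safe, feasible and acceptable to apply to ICU patients".

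**The concern.** Randomisation makes the arms comparable in expectation. It does not make them alike in any one small trial. When allocation is done correctly, every difference in an unstratified variable is chance, so an imbalance is not evidence that randomising was infeasible. Nor is a balanced baseline table evidence that it worked: patients taken out of list order or given the wrong arm would often leave the table looking unremarkable.

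Process is what a pilot could usefully learn about here. According to the section on recruitment and randomisation, an unblinded research assistant performs randomisation, outcome assessments and the intervention, and the list and envelopes are kept in the trial file as well as in the electronic system. Whether allocation followed the list under that arrangement matters to the design of the larger trial, and this row cannot show it. The risk is that a sound procedure is reported as failing, or a faulty one as feasible.

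**Working it through.** The plan gives no figure for this row, so there is none to reproduce. The check asks how often the row would give a misleading answer under several possible definitions of balance.

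**Inputs from the article.** 1:1 allocation; 16 per arm among ICU survivors; about 47 expected to be recruited, or 23 to 24 per arm if everyone randomised is compared; age and severity not stratified.

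**Assumptions.** Continuous covariates; five covariates, independent unless stated; limits of 0.25 SD, 0.5 SD or p<0.05. None of these is in the article.

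**1. Correct randomisation, one covariate.** The standardised mean difference (SMD) is about normal with mean 0 and SE = √(2/n). For n = 16, SE = √(2/16) = 0.354. P(|SMD| > c) = 2 × [1 − Φ(c/SE)].
- c = 0.25: c/SE = 0.707, P = 0.480
- c = 0.5: c/SE = 1.414, P = 0.157

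Simulation with the SD estimated gives 0.485 and 0.167.

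**2. Correct randomisation, at least one of five.** 1 − (1 − p)^5.
- c = 0.25: 1 − 0.520^5 = 0.962
- c = 0.5: 1 − 0.843^5 = 0.575

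With pairwise correlation 0.5 these fall to 0.931 and 0.476.

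**3. Correct randomisation, significance-test reading.** At least one p<0.05 among five covariates: 1 − 0.95^5 = 0.226. Such a rule passes a correct randomisation 77% of the time. With ten covariates the failure rate is 1 − 0.95^10 = 0.401.

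**4. Larger arms.** With 24 per arm, SE = √(2/24) = 0.289.

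| Limit | One covariate, n = 16 | Any of five, n = 16 | One covariate, n = 24 | Any of five, n = 24 |
|---|---|---|---|---|
| 0.25 SD | 48% | 96% | 39% | 91% |
| 0.5 SD | 16% | 58% | 8% | 35% |

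**5. Faulty allocation.** Suppose allocation has shifted one covariate by a true 0.5 SD, with 16 per arm. The two-sided t test at 5% has power 0.278, so a single p>0.05 check passes it 1 − 0.278 = 0.722 of the time. A joint check, with the other four covariates unaffected and independent, passes it 0.722 × 0.95^4 = 0.722 × 0.815 = 0.588 of the time. For a true 0.3 SD shift, the observed difference stays within 0.5 SD in Φ(0.2/0.354) − Φ(−0.8/0.354) = 0.702 of trials.

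**The case against.** The strongest reply is that balance is undefined in the article, and its definition is a detail commonly left to the SAP, which is not shown. That stands as a limit on the numbers: each is conditional on a definition that the article does not give. The Statistical analysis section plans descriptive summaries by group and says its inferential statistics are not for judging significance, so a p-value rule is only one possible reading. It does not rescue the row, because no threshold turns baseline similarity into a measure of whether allocation was carried out as planned.

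A reader might infer that the row must return a wrong verdict on a sound trial. The documents do not support that: under the 0.25 SD, 0.5 SD and p<0.05 readings, the failure rate with 16 per arm runs from a few per cent for one covariate to 96% for five. Nor would a significance-test reading almost always pass; across five covariates it passes a correct randomisation 77% of the time.

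A reader might also infer that this row alone decides whether the larger trial goes ahead. It is one of eight secondary rows, no progression rule is attached to it, the Statistical analysis section names recruitment as the main feasibility outcome, and the Discussion speaks of safety, feasibility and acceptability together.

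Two further points stand in part. Gender and site are stated stratification factors and so are partly controlled by design. A gross imbalance could hint at broken allocation, though with little power at this size.

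Finally, some process information is collected elsewhere: the percentage of eligible patients randomised, interviews about the experience of randomisation, and general monitoring of adherence. The first mixes consent with allocation, the second records experience, and the third is not tied to this criterion. None of them reports whether the list was followed.

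**Conclusion.** The concern holds in a limited form. The Randomisation row measures the wrong thing: it can, and under common definitions of balance often would, report a correct randomisation as failing, and it can pass a faulty one. The size depends on the assumed definition, the number of covariates and the arm size. It is largest for tight limits applied to several covariates and modest for a lenient limit applied to one. The fault lies in the choice of outcome measure, which the article states, and not in detail that an SAP might supply. It is worth correcting, but it does not undermine the pilot as a whole.

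**What to change.** Judge the Randomisation row by a process measure taken from the existing randomisation lists and the data capture system. Report the number and percentage of consented eligible patients who (a) were randomised, (b) were given the next assignment on the correct list for their site, and for their gender stratum if one was used, and (c) started the allocated arm. List any allocation errors. Any pass threshold is for the sponsor to set. Report baseline demographics and severity of illness by arm as description, with no pass/fail judgement and no significance test.

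The Trial status section says that recruitment was completed in February 2019. The change should therefore be made in the SAP, which the article says will be finalised before database lock, and be labelled as made after recruitment.

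The cost is one reworded row and a count from existing records, with no new patients or data collection. The drawbacks are that a pre-specified criterion is changed late and that list errors may come to light.
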